**Table 7: DRUG TRIALS TO TREAT COVID-19 (LITERATURE REVIEW***)**

| **Study** | **Investigational Drug** | **Design**  **Arms**  **Control**  **(n)** | **Duration**(days) | **Outcome** | **Adverse events** | **Remark** |
| --- | --- | --- | --- | --- | --- | --- |
| **Tang et al.^1^** | Hydroxychloroquine (HCQ)  1200mg x 3 days f/b  800mg for 2 weeks in Mild/Moderate and for 3 weeks in severe disease | Randomised, open label  2 arms,  75 SOC plus HCQ  75 SOC  (150) | 28 | 1. No difference in seroconversion rate at 28 days.  2. Significant normalisation of CRP from baseline (Absolute change 6.986 v/s 2.71, p=0.045).  3. Modest improvement in lymphopenia (p=0.546) | Diarrhoea (10% vs 0%, p=0.004) | 1.Anti virals can be confouding factors |
| **Gautret et al.^2^** | Hydroxychloroquine plus Azithromycin  HCQ 200md TID  Azithromycin 500mg on day 1 f/b 250mg day 2-5 | Retrospective observational  (80) | 10 | Beneficial effect of adding azithromycin to HCQ viral load reduction/disappearance |  | 1.No data on cardiac monitoring.  2.Small sample size.  3.Observational. |
| **Grein et al.^3^** | Remdesivir  200mg IV on day 1 f/b 100mg IV daily for 10 days | Open label, Non-randomized, Phase III  1 arm (53) | 10 | Clinical improvement seen in 68%. (36/53) | Hepatic enzyme dysfunction(23%), Diarrhoea(9), Rash(8), Renal impairment (8), Hypotension(8) | 1.Shoer duration and follow up.  2.Small size cohort  3.Not blinded or randomised |
| **Cao et al.^4^** | Lopinavir/Ritonavir  400+100mg BD | Randomised controlled, open label SOC  2 arms, 99(Lopinavir/Ritonavir+ SOC)  100(SOC) (199) | 28 | 1.Not difference in clinical improvement and mortality at the end of 28 days.  2.Do not decrease viral load/ RNA detectability | Lymphopenia(17%), Nausea(9.5%), Leucopenia(7%) | 1.Not blinded.  2. Use of steroids confounding factor |
| **Zha et al.^5^** | Corticosteroids  Methylprednisolone (MP) 40mg OD or BD for 5 days | Observational, Phase III  2 arms  11 (MP+SOC)  20(SOC) (31) |  | No difference in outcomes in patients with ARDS. Delay Viral clearance. | Liver injury (46% vs. 35%) | 1.Small size.  2.Young age group (Median age 39y) |
| **Luo et al.^6^** | Tocilizumab | Retrospective, observational | - | Significant fall in CRP and IL 6 level from baseline.  IL6 can be used for prognosis |  | 1.Use of steroids- confounding  2.Small sample  No placebo |

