# 3. RATIONALE FOR PROPOSED STUDY

The absence of specific drug treatment and lack of vaccine is a critical gap in the knowledge of COVID-19 pandemic (38). And in this regard it is important to refer to a seminal paper published on the ‘responsibility and accountability of conducting standard research including randomized clinical drug trials by the medical community’ in times of epidemics, and the authors have used the recent Ebola virus epidemic in Africa to highlight their contention (39).

The Ministry of AYUSH, GOI has recommended the self-care guidelines for preventive health measures and boosting immunity with special reference to respiratory health based on Ayurvedic literature and scientific publications. However, this advisory does not claim to be treatment for COVID-19. The role of Ayurveda Rasayana as an immunomodulator is well known and should be investigated in COVID-19 (40). In this protocol, we describe the rationale for using three Ayurveda herbal formulations individually to treat COVID-19 as an add-on/adjunct therapy to standard of care. The three Ayurveda formulations are AYUSH-64, Sanshamani Vati Plus and Yashtimadhu. In India the guidelines issues by the Ministry of Health and Family Welfare are generally followed as standard of care (See above, Section 2.6 (20). It is difficult if not impossible to expect a uniform nature of standard of care in the study site hospitals in this study.

Patients suffering from symptomatic Mild to Moderate COVID-19 will be selected for this study. By ’Mild to Moderate’ it would essentially mean that patients do not require any of the emergency measures that are advocated for severe and life-threatening cases of COVID-19. The latter would include complications of progressive lung disease, septicemia, shock and other complications (see Table 3). The mild to moderate cases of COVID-19 will belong to the categories of ‘Mild’ and ‘Pneumonia’ as described by WHO (See WHO Table on Syndromes associated with COVID-19 shown in Section 2.6 above). Mere need for supplement oxygen using non-invasive means will not negate the classification of mild to moderate COVID-19.

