# 5. STUDY DESIGN

Fig 1 shows the study flow and the overview of study design and timelines, and principal study events including clinical examinations, laboratory and other investigations.

Each of the three selected and standardized Ayurveda drugs i.e. **AYUSH 64 (A-64), Sanshamani Vati Plus (SV +)** and **Yashtimadhu (MYT)** will be assessed as add on or adjunct treatment in three different drug trials of two arms each for efficacy and safety under a common current protocol.

Each of the drug trial will be a randomized, prospective, open label, parallel efficacy, active control two arm multicentre study. Each of the three Ayurveda drugs is being considered as an adjuvant drug to Standard of Care (SOC). The SOC and Ayurveda drug combination is the experimental interventional arm which will be compared to the active control arm of standalone SOC. The total duration of each of the three drugs’ study is 12 weeks and this period includes time to clinical recovery (defined later in text) and a period of follow up to complete 12 week of observation following admission to the hospital. The nature of SOC and any follow up medication will be decided by the treating physician. Some variation in SOC between different study sites and even between patients is possible. The study investigators will meticulously record the details of SOC in the study case record form of each patient. The dose of Ayurvedic drugs is as per standard Ayurveda practise and decided by consensus amongst experts in the AYUSH working group for this patient. The total sample size of each drug study is 140 patients with 70 patients randomized to each arm.

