# CONSENT, SELECTION, SCREENING, and ENROLLMENT

Study patients will be served on first come first serve basis as per the protocol.

Consenting and eligible patients will be enrolled as soon as possible in a COCID-19 management facility and the study intervention begun. It is important that symptomatic patients suspected for COVID-19 on clinical grounds are quickly evaluated for eligibility. It is important to enroll the patient as close to the onset of symptoms as possible. As described above, this study is dealing with patients of COVID who are ‘non-emergent’ which means mild and moderate disease (pneumonia) which does not require emergency or critical care (see section on inclusion and exclusion criteria).

An ‘Patient Information Sheet’ (Appendix F) in the language understood by the patient will be provided to each patient for study and discussion prior to enrollment. The information fact sheet will describe the overall design of the study and the rationale, benefit and side effect profile of the study drug interventions, and other aspects of the study.

Patients will be selected from the outpatient or inpatient facility in COVID-19 medical centres/ hospitals. The study will be explained to the volunteer patients and those willing to sign the informed consent (Appendix G) will be screened for eligibility as per the inclusion and exclusion criteria in the protocol.

Though it will be preferable to enrol patients with diagnosis confirmed by a positive RT-PCR assay using a nasal or throat swab in a standardized procedure, a patient with a clinical diagnosis of COVID- 19 as described below will be eligible.

Eligible patients will be enrolled using a simple randomization table (provided to the investigator) in a block of 20 patients each to either of the two study arms - SOC plus Ayurveda drug or SOC. As the target sample size is 70 patients in each arm, the first block of randomized allocation will be of 10. The study randomization will be carried out by the investigator.

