# 10. PATIENT POPULATION

The patients will be largely drawn from COVID-19 clinics and outpatients in various medical colleges and hospitals. All patients will be admitted in the hospital for standard care and those willing to participate in the study will be screened and enrolled as described above. Only patients with mild to moderately severe symptoms will be selected as described above. If the patients progress to a severe stage of illness as described below, they will be withdrawn from the study but the investigator will be encouraged to follow the patient ill study completion at week 12 and during this period record the hospital management, course of illness , final outcome and post recovery health status as described in this protocol.

- 1. Inclusion Criteria:

1. Typical Clinical presentation of acute onset febrile illness with cough and a RT_PCR based laboratory confirmation test for COVID-19
2. Patients with either sex, 21to 69years age
3. Patients with Mild to Moderate COVID-19 as described below
4. All patients must agree not to share medication
5. Patients willing to participate and sign an informed consent
   Note: The criteria for mild to moderate COVID-19 are based on the WHO recommendations (See Section 2.5 above with WHO Table on clinical syndromes of COVID-19 and include Mild disease and Uncomplicated Pneumonia but not severe disease which requires any form of intensive care such as invasive techniques for supplemental oxygen or ventilation and life support systems, and absence of any life threatening complications (such as severe respiratory failure, adult respiratory distress syndrome, septicaemia shock and other complications shown in Table 3 above)
   1. Exclusion Criteria

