# 13. LABORATORY & OTHER INVESTIGATIONS

These are common to the each of the three Ayurveda formulation drug trials:

1. Blood/Serum (routine): Haemogram, Platelet count, Total leukocyte differential count, Hemoglobin and ESR, Blood sugar level (Fasting), Liver function test and Liver Enzymes (SGOT,SGPT, Alkaline Phosphatase), Renal functions (Serum creatinine, Blood Urea Nitrogen), Lipid profile (Total cholesterol, HDL cholesterol, LDL cholesterol, Triglycerides, VLDL)
2. Serum (inflammatory markers, organ damage):C-Reactive protein titer, lactate dehydrogenase, ferritin, Pro-Calcitonin, Troponin, D-Dimer,
3. Special tests: Blood for Vitamin D, Vitamin B12, Oxidation Biomarkers (Superoxide Dismutase (SOD), Glutathoine (GSH)
4. Cytokine Panel: Interleukin (IL) IL-2, IL-1 beta, IL-4, IL-6,IL-10, IL-13, IL-17, TNF-α, Monocyte Chemotactic Protein-1 (MCP), Interferon gamma, TGF-bet
5. Serum Protective Antibody Response: IgM and IgG against SARS-CoV-2
6. Routine Urinalysis, Urine Pregnancy Test for women of child bearing potential
7. Confirmatory Diagnostic Test: Nasal and/or Throat swab for real time RT-PCR for SARS-CoV-2 (See Appendix O)
8. Other Investigations: USG Abdomen and Pelvis, ECHO-Color Doppler and 12 Lead ECG

Chest X-ray, HRCT scan Chest

**13.1** Rationale for Cytokine Assay: Cytokine assay can be used to study important anti-viral effects (gamma interferon), immune mediated inflammation (IL-6, anti-TNF, IL-17), TH 1 and TH 2 immune response and antibody producing B cell activity (Il 4, IL 13), activation of immune cells such as macrophage activation (MCP). Intense up regulation and elevation of IL 6 and several other cytokines has been reported by several clinical case series and research in COVID-19 and can guide specific therapy (as in case of use of monoclonal antibody to IL-6 receptor being used to treat Cytokine storm in COVID 19).

Detail methods for diagnostic tests, serology and cytokine assay are described in Appendix O.

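### Expected site differences in standard of care enter the primary comparison as avoidable noise, and background therapy that comes to differ by arm is only partly visible

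*Combined protocol and SAP*

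**What the plan says.** Section 5 defines the contrast: "The SOC and Ayurveda drug combination is the experimental interventional arm which will be compared to the active control arm of standalone SOC". It leaves the content of SOC open: "The nature of SOC and any follow up medication will be decided by the treating physician". It expects variation: "Some variation in SOC between different study sites and even between patients is possible". Section 3 is firmer: "It is difficult if not impossible to expect a uniform nature of standard of care in the study site hospitals in this study".

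Allocation is described in the section on consent, selection, screening and enrolment. It uses a "simple randomization table (provided to the investigator) in a block of 20 patients each to either of the two study arms", with a first block of 10 explained by the target of 70 per arm. The investigator carries it out. No site stratum is mentioned.

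Section 17.2 compares mean time to recovery by ANOVA and the proportion recovered by a two-proportion z-test. Neither test is given a site or SOC term, and regression is reserved for finding predictors of outcome.

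SOC is to be recorded. Sections 5 and 16 send its details to the case record form. Appendix H has a generic concomitant-therapy table with start and end dates. The daily report in Appendix J has a row for steroid and rows for oxygen, intubation, ventilator and ICU, but none for antivirals, hydroxychloroquine/azithromycin or anti-IL-6 therapy. Section 11.2 lists steroid use among the secondary outcomes. No analysis brings the SOC record into the primary comparison of arms.

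**The concern.** Two separate problems arise from the same feature.

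**Noise.** If hospitals treat differently, mean recovery time will differ between them. A list not balanced within site leaves chance differences in the site mix of the arms, and a test without site counts the between-site spread as error. The trial then loses precision it could keep at almost no cost.

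**Bias.** The treating physician is not blinded. If knowledge of the arm leads to more, or less, effective background therapy in one arm, the contrast mixes that therapy with the study drug. Blinded assessment of recovery does not protect against this, because a patient who receives an effective extra treatment really does recover sooner. The protocol knows the hazard: in Table 7 it remarks on a randomised add-on trial against SOC, "Use of steroids confounding factor", and makes a similar remark about antivirals in another.

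**Working it through.** **1. The plan's own figures.** The sample size is by convenience (Section 17.1), so there is no power calculation to reproduce. The totals agree: 2 x 70 = 140. The block layout reaches the target only if blocks are counted per arm: 10 + 3 x 20 = 70. Counted in total patients, (140 - 10)/20 = 6.5 blocks, which is not whole. The layout therefore fits one trial-wide list, though the text does not say so outright.

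**2. Standard error.** The protocol gives no SD for recovery time. Table 2 reports, for one hospital cohort, a median of 10 days with IQR 7-14. Assuming approximate normality, SD = (14 - 7)/1.349 = 5.19 days. With 70 per arm, SE = 5.19 x sqrt(2/70) = 0.88 days. The difference detectable with 80% power is 2.46 days.

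**3. Site differences (noise).** For K equal sites whose means have SD t, under one list that ignores site, the variance of the unadjusted difference is about (4/140) x [5.19² + t² x (K-1)/K]. For t = 3 and K = 4 this is (4/140) x (26.9 + 6.75) = 0.96, so SE is 0.98 days. Simulation (8,000 trials per setting, blocks of 10 and then 3 x 20 per arm) agrees:

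| Site SD | Sites | SE without site | SE with site | Variance ratio |
|---|---|---|---|---|
| 3 days | 4 | 0.985 | 0.889 | 1.23 |
| 3 days | 6 | 0.990 | 0.878 | 1.27 |
| 1.5 days | 4-6 | - | - | 1.03-1.04 |

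A ratio of 1.23-1.27 is equivalent to discarding 1 - 1/1.23 = 19% to 1 - 1/1.27 = 21% of the patients.

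A second simulation, with 3, 5 or 7 equal sites, gives power for a true 2.5-day effect:

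| Site SD | One list, no site term | List by site plus site term |
|---|---|---|
| 1 day | 0.80 | 0.80-0.82 |
| 2 days | 0.75-0.76 | 0.81-0.82 |
| 4 days | 0.60-0.61 | 0.80-0.82 |

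With one list and no site term the type I error stayed at 4.7-5.6% and the mean bias was about zero. Most of the gain comes from the site term. At a site SD of 4 days, a list by site analysed without the term reached only 0.62-0.64, with a type I error of 1.2-1.4%.

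**4. Care that differs by arm (bias).** Bias = q x D, where q is the between-arm difference in use of an effective background therapy and D is the days it saves. Both are assumed. For scale, steroid use in the cohorts of Table 6 runs from 19% to 45%. The two-sided 5% test is evaluated with SE 0.88 and no true drug effect.

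| q | D | Bias | Rejects, either direction | Falsely favours drug if extra therapy is in the drug arm | Falsely favours drug if extra therapy is in the SOC arm |
|---|---|---|---|---|---|
| 10 points | 2 days | 0.2 days | 5.6% | 4.2% | 1.4% |
| 20 points | 3 days | 0.6 days | 10.5% | 10.1% | 0.4% |
| 30 points | 4 days | 1.2 days | 27.7% | 27.7% | 0.04% |

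When the extra therapy goes to the SOC arm, the harm is a masked effect. Power for a true 2.5 days falls from 81% to 75% at a bias of 0.2 days and to 58% at 0.6 days. A site term changes none of this, because the difference arises between arms within a site.

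**The case against.** Locally chosen SOC is normal in a pragmatic add-on trial, and this one is declared exploratory and unpowered, so no stated power is lost. Under valid randomisation, site differences do not create a false effect. The plan also records more than a quick reading suggests: Section 16 asks for drug, dose and duration of SOC, Section 7 has hospital data extracted daily, and Section 11.2 makes steroid use a secondary outcome, compared between arms under Section 17.2. All of that stands. It limits the first problem to precision and means that the steroid route is already partly visible.

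Four stronger readings are not supported.

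- A reader might infer that SOC is chosen only after allocation. Section 10 says "All patients will be admitted in the hospital for standard care and those willing to participate in the study will be screened and enrolled", so SOC can begin before allocation and change after it.
- A reader might infer from Section 13.1 that the trial's own cytokine results will steer treatment, since such assays "can guide specific therapy (as in case of use of monoclonal antibody to IL-6 receptor being used to treat Cytokine storm in COVID 19". That sentence is a rationale drawn from published reports, not a plan to treat on trial results.
- A reader might take Section 2.6 as saying that steroids shorten recovery. It adds that evidence is lacking and does not recommend routine use.
- A reader might wish to leave out CRP and IL-6 values taken after steroid or anti-IL-6 treatment starts. That conditions on treatment given after randomisation, which the study drug may itself alter, and could add bias.

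**Conclusion.** The point holds in two limited parts.

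**Precision.** The plan expects SOC to differ between sites, yet its primary tests ignore site and its allocation text names no site stratum. The avoidable increase in variance is about 3-4% at a site SD of 1.5 days and about 23-27% at 3 days. It is not a source of systematic bias. That the list is not by site rests on silence plus the block arithmetic.

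**Possible bias.** Nothing blinds the treating physician, and the forms have no dedicated daily row for any background drug except steroid. A between-arm difference in effective therapy could move the contrast by about 0.2-1.2 days either way, against an SE of 0.88 days. The documents do not show that this will happen, only that the plan would not show it well.

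Site number, site SDs, q and D are assumptions, and the 5.2-day SD is borrowed from one cohort. The conclusion also presumes randomisation. The opening of Section 17 calls the study non-randomised, against the title and Section 5, and those passages must be reconciled.

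**What to change.** 1. Generate the allocation list separately for each site in small blocks, and include site in the primary comparison: a linear model with arm and site for recovery time, and a site-stratified comparison such as Cochran-Mantel-Haenszel for the proportion recovered. State beforehand how very small sites are pooled.
2. Record the SOC in place at baseline before the allocation is opened. Add dated rows to the daily form for antiviral, hydroxychloroquine/azithromycin and anti-IL-6 therapy (steroid is already there), and report use of each class by arm beside the primary result. This makes differential care visible; it does not remove its effect.
3. Keep the all-patients comparison of CRP and IL-6 as the main one. Any analysis that accounts for values after steroid or anti-IL-6 start should be prespecified and supplementary only.

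The cost is a set of site lists, one baseline entry per patient, a few form rows and one model term. The downside is minor paperwork and the pooling of very small sites. The physician's choice of care is untouched.

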**Fig 1: Study Flow diagram showing Study Events and Timelines**

Screening of Voluntary and Consenting In-patients suffering from Mild to Moderately Severe COVID-19 for Eligibility as per Inclusion-Exclusion Criteria

3 Ayurveda formulation drug trial studies under a common protocol

(Separate study for each AYUSH 64 / Yashtimadhu / Samshamai Vati Plus)

Randomize Eligible Hospitalized Patients

(Open Label, Parallel Efficacy, Active Control Standard of Care (SOC), Two Arm Study)

Selected Ayurveda Formulation (Adjuvant) Versus SOC (Active Control)

Time Points

Clinical Assessment

Investigations

Baseline

Case Record Form (CRF), Medical History Clinical Examination, Ayurveda Assessment, Health Status (WHOQs), QoL (HR-BHF)

Diagnostic (PCR), Serology (IgM, IgG), Routine Hematology Profile, Special Assays, X-Ray Chest & Imaging, ECG

Week 4

Brief Clin Exam, Ayu Exam, Health Status (WHO- Qs) & QoL (HR-BHF Qs), Adverse Events (AEs)

Diagnostic (PCR), Serology (IgM, IgG), Routine haematology Body Profile, Special Assays

Week 8

Brief Clin Exam, Ayu Exam, Health Status (WHO- Qs) & QoL (HR-BHF Qs), Adverse Events (AEs)

Diagnostic (PCR), Serology (IgM, IgG), Routine haematology Body Profile, Special Assays

Week 12

Completion Outcome Assessment, CRF Clin Exam, Ayu Exam, WHO- Qs & QoL (HR-BHF Qs), AEs

Diagnostic (PCR), Serology (IgM, IgG), Routine haematology Body Profile, Special Assays

***Further Assessment Time Points**: (i) During Hospitalization: Daily monitored vital parameters, disease symptoms, disease progression and recovery, and investigations carried out as per protocol till DISCHARGE; Laboratory and Imaging investigations as per protocol but the study investigator and treating physician can do any additional test as per their judgment (ii)Post DISCHARGE: Daily Telephonic Contact using a special mobile phone application for any relapse or any other symptoms or complications or any other Issue (iii) Discharge: Complete all formalities as required for study completion (iv) Skip week 4 or week 8 end point evaluation within 2 weeks of DISCHARGE

The total study period is 12 weeks; Primary Efficacy is ‘Clinical Recovery’ as described in the protocol; Study participant developing severe COVID 19 or severe complication and requiring special critical support/ ICU/ ventilator support will be withdrawn from the study but followed up to record outcome; Both Ayurvedic and Allopathic Physicians will jointly examine and monitor study participants in addition to the hospital treating physician.

Patients will be selected from the outpatient or inpatient facility in COVID-19 medical centres/hospitals. The study will be explained to the volunteer patients and those willing to sign the informed consent will be screened for eligibility as per the inclusion and exclusion criteria in the protocol. Patient suffering from severe COVID-19 will be excluded (see exclusion criteria below).

